**Table 2: Clinical Laboratory Evaluations**

|                           |                                             |
|---------------------------|---------------------------------------------|
| Hematology         |                                             |
| Hemoglobin                | Platelet count                              |
| Hematocrit                | WBC count with differential                 |
| RBC count                 | High sensitivity C-reactive protein (hsCRP) |
| Reticulocyte count        |                                             |
| Serum Chemistry    |                                             |
| Blood urea nitrogen       | ALT (SGPT)                                  |
| Creatinine                | AST (SGOT)                                  |
| Electrolytes with glucose | Total and Direct bilirubin                  |
|                           | Lactate dehydrogenase (LDH)                 |

|                                                                                                                                           |                    |
|-------------------------------------------------------------------------------------------------------------------------------------------|--------------------|
| Urinalysis                                                                                                                         |                    |
| pH                                                                                                                                        | Bilirubin          |
| Specific gravity                                                                                                                          | Blood              |
| Protein                                                                                                                                   | Nitrite            |
| Glucose                                                                                                                                   | Urobilinogen       |
| Ketones                                                                                                                                   | Leukocyte esterase |
| If urinalysis is positive for blood or leukocyte esterase, a microscopic examination for RBC, WBC, bacteria, and casts will be performed. |                    |

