### 6.2.5 Review to Determine Next Dose Level

When 4 subjects have been studied (in any level) at the individual site, the data for these subjects will be reviewed by the investigator and Medical Monitor in order to determine the next dose to be administered. The data for the first 48 hours for each subject, as available, will be reviewed.

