## **7.2 Reporting**

All AEs occurring during this clinical trial will be recorded. The investigator will review each event and assess its relationship to drug treatment (unrelated, remote, possible, probable, or definite). Worsening of pre-treatment events after initiation of investigational product must be recorded as new AEs.

Each sign or symptom reported will be graded in accordance with the WHO Common Toxicity Criteria (Appendix 1) where Grade 1 = mild, Grade 2 = moderate, Grade 3 = severe, Grade 4 = life-threatening or disabling, and Grade 5 = death related to AE. The date of AE onset, time of onset, duration, severity, relationship, outcome, and use of concomitant treatment will be recorded for each event.

For the purposes of this study, VOC shall be defined as an episode requiring a visit to a medical facility resulting in medical treatment for pain. It is recognized that VOC and pain are frequent and expected events in SCD, and the use of narcotics for these episodes is often required and considered routine. When determining grade of an AE for VOC or pain, the investigator shall use the following classification (noted below), rather than the need for narcotics as described in the WHO Common Toxicity Criteria.

If the AE does not have a toxicity grade listed in Appendix 1, the following severity classifications will be used.

- Mild - The AE is easily tolerated and does not interfere with daily activity
- Moderate - The AE interferes with daily activity, but the subject is still able to function
- Severe - The AE is incapacitating and requires medical intervention

The relationship of each AE to study drug will be assessed using the following definitions:

Definite:

- Distinct temporal relationship with drug treatment
- Event cannot be explained by subject's clinical state or other factors

Probable:

- Reasonable temporal relationship with drug treatment
- Event cannot easily be explained by subject's clinical state or other factors

Possible:

- Reasonable temporal relationship with drug treatment
- Event could be explained by subject's clinical state or other factors

Remote:

- Poor temporal relationship with drug treatment
- Event easily explained by subject's clinical state or other factors

Unrelated:

- Event occurring before dosing
- Event or intercurrent illness due wholly to factors other than drug treatment

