#### **7.4 Dose Limiting Toxicities and Study Stopping Rules**

Dose-limiting toxicity will be defined as TEAEs of severity Grade 3-5 deemed by the investigator to be related to GMI-1070 per the AE section of this protocol (Sections 7.1 Monitoring, and 7.2, Reporting). For the purpose of determining Dose Limiting Toxicity, related AEs shall include “probably related” and “definitely related” as determined by the investigator. AEs will be graded according to the WHO Common Toxicity Criteria, or by severity of AE if not included in the WHO Criteria, as described in Section 7.2. Thus, the study will be temporarily halted for further review of safety data according to the following guidelines for toxicities deemed to be related to GMI-1070:

- If at least 2 Grade 3 events are observed in 1 subject.
- If at least 3 Grade 3 events are observed within a given dose level.
- If a Grade 4 or Grade 5 event is observed.
- If at least 2 subjects experience a VOC within 24 hours of receiving GMI-1070. A VOC is defined as an episode requiring a visit to a medical facility resulting in medical treatment for pain.

In addition, the study may be halted for further review:

- If, for any reason involving safety, the investigator deems continuing the study inappropriate.
- If, for any reason, the Sponsor deems continuing the study inappropriate.

Dosing will be halted in the event of unacceptable AEs as described above. Further review of the study data will be undertaken in this situation, and the action to be taken with the study will be determined together by the investigator and Sponsor.

If the study is halted temporarily or terminated, a written statement fully documenting the reasons for study halt or termination will be provided to the IRB.

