**Cardiac**

| Toxicity      | Grade 0    | Grade 1                                                                                                            | Grade 2                                                                                                            | Grade 3                                                                       | Grade 4                                                                  |
|----------------------|-------------------|---------------------------------------------------------------------------------------------------------------------------|---------------------------------------------------------------------------------------------------------------------------|--------------------------------------------------------------------------------------|---------------------------------------------------------------------------------|
| Cardiac arrhythmias  | none              | asymptomatic, transient, requiring no therapy                                                                             | recurrent or persistent, no therapy required                                                                              | requires treatment                                                                   | requires monitoring; or hypotension, or ventricular tachycardia or fibrillation |
| Cardiac function     | none              | asymptomatic, decline of resting ejection fraction by less than 20 % of baseline value                                    | asymptomatic, decline of resting ejection fraction by more than 20% of baseline value                                     | mild CHF, responsive to therapy                                                      | severe or refractory CHF                                                        |
| Cardiac ischemia     | none              | non-specific T- wave flattening                                                                                           | asymptomatic, ST and T wave changes suggesting ischemia                                                                   | angina without evidence of infarction                                                | acute myocardial infarction                                                     |

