| Cardiac- pericardial | none              | asymptomatic effusion, no intervention required                                                                           | pericarditis (rub, chest pain, ECG changes)                                                                               | symptomatic effusion; drainage required                                              | tamponade; drainage urgently required                                           |
| Hypertension         | none or no change | asymptomatic, transient increase by greater than 20 mm Hg (D) or to > 150 / 100 if previously WNL. No treatment required. | recurrent or persistent increase by greater than 20 mm HG (D) or to > 150 / 100 if previously WNL. No treatment required. | requires therapy                                                                     | hypertensive crisis                                                             |
| Hypotension          | none or no change | changes requiring no therapy (including transient orthostatic hypotension)                                                | requires fluid replacement or other therapy but not hospitalization                                                       | requires therapy and hospitalization; resolves within 48 hours of stopping the agent | requires therapy and hospitalization for > 48 hours after stopping the agent    |

Abbreviations: PFT=pulmonary function test, CHF=congestive heart failure,.

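### Laboratory adverse events with no Appendix 1 grade reach Grade 3 only if incapacitating, so a symptomless, urgently treated change does not count as a dose-limiting toxicity

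*Protocol*

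**What the plan says.** Four parts of the protocol bear on this point.

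- **What is measured.** Table 2 lists "Electrolytes with glucose" under serum chemistry. Table 1 schedules chemistry at screening, at baseline, on Days 2 and 3 and on Day 7. The 8-hour draw is hematology only. Section 7.1 allows an abnormal laboratory finding to be an adverse event.
- **How it is graded.** Section 7.2 grades events by Appendix 1 and gives general meanings for the grades, from mild (Grade 1) to severe (Grade 3), then "Grade 4 = life-threatening or disabling, and Grade 5 = death related to AE". For events outside the appendix: "If the AE does not have a toxicity grade listed in Appendix 1, the following severity classifications will be used". Mild and Moderate are defined by tolerability and daily activity. The last level is "Severe - The AE is incapacitating and requires medical intervention".
- **What the grade triggers.** Section 7.4 defines a DLT as a Grade 3-5 treatment-emergent event judged probably or definitely related. Events are graded by the WHO criteria "or by severity of AE if not included in the WHO Criteria, as described in Section 7.2". The grade-based halts are two related Grade 3 events in one subject, three within a dose level, or one Grade 4 or 5 event.
- **How the next dose is chosen.** Section 6.2.5 says: "The data for the first 48 hours for each subject, as available, will be reviewed". If a DLT is seen, safety data decide. If none is seen, effect data decide.

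**The concern.** The fallback scale asks how a patient feels and functions. That suits symptoms but not laboratory values, which can need urgent correction while the patient notices nothing. Because Severe requires incapacity as well as intervention, such an event cannot reach Grade 3 through the fallback list.

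The grade decides which branch of 6.2.5 applies. With a DLT, the options named are a lower dose level or a halt for review. Without one, the dose may stay the same or go up if no blood flow effect is clearly detectable, and may stay the same or go down if one is. A site joining later may also start at the level chosen. Safety is the primary objective, so the rule that separates these branches should capture a related event needing urgent treatment.

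**Working it through.** The protocol states no figure for this point, and no sample size or error rate is involved. The check is a reading of the grading rules against the scheduled tests.

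**1. Is there an Appendix 1 row?** The metabolic block covers high and low glucose, amylase, high and low calcium, and low magnesium. No block of the appendix has a sodium or potassium row. Table 2 does not name the ions in the panel; that sodium and potassium are among them is an assumption.

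**2. Apply the fallback.** Take a potassium change that is clinically significant, probably related, symptomless, urgently treated and not life-threatening.

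- Severe needs two conditions. Medical intervention is met; incapacity is not.
- With no effect on daily activity, the event is Mild. If the treatment itself disrupts the day, it is at most Moderate.
- The result is below Grade 3.

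**3. Apply 7.4.** The event is not a DLT and adds 0 to both Grade 3 counts.

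**4. Compare events that do have a row.**

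| Event | Appendix 1, Grade 3 | Incapacity needed? |
|---|---|---|
| High glucose, no symptoms | 251-500 mg/dL | No |
| Creatinine | 3.1-6.0 times normal | No |
| Transaminases | 5.1-20.0 times normal | No |
| Arrhythmia | "requires treatment" | No |
| Hypertension | "requires therapy" | No |
| Sodium or potassium | no row; 7.2 fallback | Yes |

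The three laboratory tests in the first rows are all in Table 2. A silent glucose of 300 mg/dL is Grade 3, while a silent potassium change needing urgent treatment is not. The only difference is whether a row exists. If the potassium change caused an arrhythmia needing treatment, the arrhythmia would be Grade 3 under its own row, but only after the complication had occurred.

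**5. Effect on the rules, with assumed events.** Suppose three subjects at one dose level each have one such event.

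- Present text: 3 × 0 = 0 Grade 3 events, so no DLT and no grade-based halt.
- With these events graded Severe: 3 × 1 = 3 Grade 3 events, so a DLT is present and the limit of three in a dose level is met.

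This shows how the rule works. It is not a forecast.

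**The case against.** The strongest reply is that very little escapes, and much of it stands.

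- **Grade 4 is available.** The fallback list carries no grade numbers. The sentence that makes severe equal Grade 3 also defines Grades 4 and 5, and 7.4 speaks of Grades 3-5 without capping unlisted events. It would be inconsistent to use that sentence for Grade 3 and not for Grade 4. A reader might infer that even a life-threatening potassium value goes uncounted; the text does not support that. It is best read as Grade 4, and one related event then halts the study. What remains is the urgent but not life-threatening change.
- **The event would be seen.** A reader might also infer that it is hidden from those choosing the dose. It is not. Table 3 puts clinical laboratory data in the review, and the synopsis requires consensus on safety before the study proceeds. Section 6.2.1.4 calls for unexpected abnormal values to be repeated until confirmed, explained or resolved. Section 7.3 makes important medical events reportable as serious, and 7.4 allows halts on judgment. These safeguards limit the harm, but none makes the event a DLT. Table 3 says the safety data are reviewed to determine whether a DLT has occurred, and that definition leaves this event out.
- **Size.** Counting sodium and potassium results over the study would look large but would measure nothing relevant. Only adverse events are graded, and 6.2.1.4 does not treat out-of-range results as abnormal unless the investigator finds them clinically significant. Nor does the total number of Appendix 1 rows graded by value help, since several concern tests that Table 2 does not list, such as coagulation and amylase. The protocol reports no electrolyte signal, and all adverse events in the 72 healthy subjects (54 active, 18 placebo) were Grade 1 or 2.
- **Judgment remains.** Words such as urgent and clinically significant still rest with the investigator, as does relatedness. That is true, but an investigator who judges an event urgent and related should then be able to grade it so that it counts.

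**Conclusion.** The point holds in a narrow form. For a laboratory event without an Appendix 1 row, 7.2 places a related, symptomless, urgently treated and not life-threatening change below Grade 3. It therefore stays outside the DLT definition and the Grade 3 halting counts, and 6.2.5 may send the dose decision to effect data. The protocol treats comparable listed events differently and gives no reason.

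No probability can be attached to this. Such events are probably rare, and other safeguards would bring them to the reviewers' attention. What is missing is the automatic trigger. The conclusion assumes that the electrolyte panel includes sodium and potassium and that the 7.2 definition of Severe is applied as written. The point does not depend on the SAP, because DLT grading and halting are fixed in the protocol and operate during dosing. It is an inexpensive improvement, not a sign that the trial is unsafe.

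**What to change.** Add two sentences to section 7.2, to this effect:

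> *For a laboratory adverse event without an Appendix 1 grade, a clinically significant change from the subject's own baseline that needs urgent medical intervention (not routine oral supplementation) is Severe (Grade 3) even without symptoms. Grades 4 and 5 also apply to adverse events not listed in Appendix 1.*

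Keep the first sentence to laboratory events. Replacing the word joining the two conditions of Severe would also change the grading of vaso-occlusive crisis and pain, which 7.2 sends to the same list. A crisis by definition involves medical treatment, so every one would become Severe.

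Numeric sodium and potassium grades in Appendix 1 are optional; they would make the grade independent of judgment. LDH, reticulocytes and hsCRP need none.

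The cost is a protocol amendment with Sponsor, investigator and IRB approval, and no new tests. One such event would become a DLT and move that dose decision to safety data, so an occasional extra safety-based review is possible. A grade-based halt would still need two related Grade 3 events in one subject, three in a dose level, or one of Grade 4 or 5.

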### **7.3 Serious Adverse Event**

An SAE is any untoward medical occurrence that (by WHO and ICH definitions):

- Results in death
- Is life-threatening
- Results in permanently disabling or incapacitating condition
- Requires inpatient hospitalization
- Prolongs inpatient hospitalization
- Is a congenital anomaly/birth defect
- In addition, is an important medical event that may not result in death, be life-threatening, or require hospitalization but which, based upon appropriate medical judgment, may jeopardize that subject and may require medical or surgical intervention

All SAEs will be reported to the CRO SAE Hotline within 1 working day and followed by written reports within 2 working days, whether or not the SAEs are deemed drug-related.

If an SAE occurs, the following CRO SAE Hotline is to be contacted immediately:

SAE [contact]

SAE [contact]

The initial report of an SAE should include the following minimum information: an identifiable subject; the investigational product; an identifiable reporting source; and an event or outcome that can be identified as serious. The investigator or designee must also inform the IRB, in compliance with GCP and local IRB reporting guidelines, of an SAE, whether or not considered study-related. The initial written report to the CRO and to the IRB must be as complete as possible.

Questions regarding safety issues and any SAEs may be directed to the Medical Monitor:

[name], FAAP  
Vice President, Clinical Development  
GlycoMimetics, Inc.

Office [contact]

Office [contact]

24-Hour Contact Number (cell phone): [contact]

E-mail: [contact]

The Sponsor will be responsible for reporting SAEs to the Food and Drug Administration as required.

#### **7.4 Dose Limiting Toxicities and Study Stopping Rules**

Dose-limiting toxicity will be defined as TEAEs of severity Grade 3-5 deemed by the investigator to be related to GMI-1070 per the AE section of this protocol (Sections 7.1 Monitoring, and 7.2, Reporting). For the purpose of determining Dose Limiting Toxicity, related AEs shall include “probably related” and “definitely related” as determined by the investigator. AEs will be graded according to the WHO Common Toxicity Criteria, or by severity of AE if not included in the WHO Criteria, as described in Section 7.2. Thus, the study will be temporarily halted for further review of safety data according to the following guidelines for toxicities deemed to be related to GMI-1070:

- If at least 2 Grade 3 events are observed in 1 subject.
- If at least 3 Grade 3 events are observed within a given dose level.
- If a Grade 4 or Grade 5 event is observed.
- If at least 2 subjects experience a VOC within 24 hours of receiving GMI-1070. A VOC is defined as an episode requiring a visit to a medical facility resulting in medical treatment for pain.

In addition, the study may be halted for further review:

- If, for any reason involving safety, the investigator deems continuing the study inappropriate.
- If, for any reason, the Sponsor deems continuing the study inappropriate.

Dosing will be halted in the event of unacceptable AEs as described above. Further review of the study data will be undertaken in this situation, and the action to be taken with the study will be determined together by the investigator and Sponsor.

If the study is halted temporarily or terminated, a written statement fully documenting the reasons for study halt or termination will be provided to the IRB.

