## **5 STUDY AND CONCOMITANT TREATMENTS**

### **5.1 GMI-1070**

The official product name, as indicated in the Investigator's Brochure, is 'GMI-1070 Injection, 30 mg/mL.' However, in order to allay any confusion regarding the route of administration in this protocol, the product has been referred to as 'GMI-1070.' For further details regarding the exact composition of the product, please refer to the Investigator's Brochure.

Investigational product will be supplied in vials, each containing 250 mg of liquid formulation of GMI-1070 at a 30 mg/mL concentration. Each study drug administration will occur over a period of 20 minutes from the start of the IV infusion, and will be followed by a saline flush.

The test product will be administered using 1 of the following dose regimens (2 doses total, administered at 0 and 10 ± 1 hours):

- Dose Level A, 20 mg/kg load followed by 10 mg/kg at 10 ± 1 hours
- Dose Level B, 40 mg/kg load followed by 20 mg/kg at 10 ± 1 hours
- Dose Level C, 10 mg/kg load followed by 5 mg/kg at 10 ± 1 hours
- Dose Level D, 5 mg/kg load followed by 2.5 mg/kg at 10 ± 1 hours

A written authorization (prescription/order/instruction) signed by an appropriately licensed physician, in this case the investigator, is required prior to providing any subject with investigational product.

Note: If enrollment at a site begins after other sites have enrolled in the study, the safety, PK, and blood flow information gained by early-enrolling site(s) may be used to modify dosing by later-enrolling site(s).

After Dose Level A has been administered to at least 4 subjects at one site, and this site's investigator and the Medical Monitor have determined it appropriate to proceed with another dose level as described above, a new site joining the study may proceed with either of the confirmed dose levels (Dose Level A, or the subsequent chosen dose level) if agreed by the new site's investigator and Medical Monitor.

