**Table 3: Data Reviewed to Determine Next Dose Level**

|                        | Safety                                         | PK                                            | Effect                                        |
|------------------------|-------------------------------------------------------|------------------------------------------------------|------------------------------------------------------|
| Data to review: | Physical examination, AEs, clinical labs, vital signs | GMI-1070 plasma levels                               | IVM data                                             |
| To determine:   | If dose-limiting toxicity is seen*                    | If plasma levels are consistent with expected levels | If difference in IVM data is seen pre- and post-dose |

\*Dose-limiting toxicity is defined in Section 7.4.

Based on review of these data, and determination of the above, dosing may continue as follows using 1 of the dose levels described in this protocol:

- If dose-limiting toxicity is seen, the decision will be made based on safety data.
  - If dose-limiting toxicity is seen, and continued dosing at a lower dose level is believed to be appropriate (as determined by the investigator and Medical Monitor), the study may continue at a lower dose level.
  - If dose-limiting toxicity is seen, and continued dosing at any level is not warranted (as determined by the investigator and Medical Monitor), the study will be halted for further review of the data.
- If no dose-limiting toxicity is seen, the decision will be made based on effect data.
  - If a microvascular blood flow effect is not clearly detectable by IVM, the study may continue at the same dose to gather more data, or increase to a higher dose level.
  - If a microvascular blood flow effect is clearly detectable, the study may continue at the same dose, or decrease to a lower dose level.

Any individual site safety concerns discussed, that could have a more global impact, will be shared among all participating sites.

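### The VOC halt in Section 7.4 sits under a lead-in limited to drug-related toxicity with no exemption, so a mandatory safety trigger is ambiguously drafted and may be weakened by investigator attribution

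*Protocol*

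**What the plan says.** Section 7.4 defines dose-limiting toxicity (DLT) as Grade 3 to 5 treatment-emergent events that the investigator judges related to GMI-1070. It then says what related means, opening with "For the purpose of determining Dose Limiting Toxicity, related AEs shall include" and naming only the probable and definite categories. The next step, introduced by the word Thus, is a temporary halt under the "following guidelines for toxicities deemed to be related to GMI-1070". Four bullets follow. Three count graded events. The fourth reads "If at least 2 subjects experience a VOC within 24 hours of receiving GMI-1070" and is followed by a definition of VOC as a facility visit with medical treatment for pain, without any grade or causality element. A separate list gives the investigator and the sponsor discretion to halt.

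Section 7.2 supplies the attribution scale. An event belongs to the possible category if the timing is reasonable and "Event could be explained by subject's clinical state or other factors". The same section says "It is recognized that VOC and pain are frequent and expected events in SCD". Section 9.2.4, for the safety summaries, counts possible, probable and definite all as drug-related.

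Section 5.1 gives the dosing as "2 doses total, administered at 0 and 10 ± 1 hours". Section 6.2.5 provides that, after each four subjects at a site, "the data for these subjects will be reviewed by the investigator and Medical Monitor".

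**The concern.** Safety is the primary objective, and VOC is the only clinical event that Section 7.4 singles out with a trigger of its own. A new crisis soon after dosing is the harm one would most want to catch in stable sickle cell patients. It is also the event that attribution handles worst. It is typical of the disease, the study is open-label and not randomized (Section 5.1.1), and each rating is one investigator's judgment. If the lead-in applies, two early VOCs could pass without a mandatory halt because one of them was put down to the underlying disease.

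The wording leaves two further points open. It does not settle whether a VOC rated possible counts. The probable/definite limit is stated for DLT, yet the halt list follows from it by Thus, and Section 9.2.4 uses the wider meaning. Nor does the bullet say whether the 24 hours run from the first dose only or from either dose.

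**Working it through.** The protocol states no operating characteristic for this rule, so there is no figure to reproduce. The calculations below are illustrations.

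**Inputs from the protocol.** Total sample 20, in groups of 4 (Sections 3 and 4.1). Threshold: 2 subjects (Section 7.4). Doses at 0 and 10 ± 1 hours (Section 5.1), so the window ends at 24 hours if it runs from the first dose, or at 33 to 35 hours after the first dose if it also runs from the second. About 60% of SCD-SS patients have at least one severe VOC per year (Section 1.2).

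**Assumptions.** The true early-VOC risk r and the share q of early VOCs that count toward the halt. Neither is in the documents.

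**1. Chance of a halt.** With p = r × q, P(halt) = 1 − (1 − p)^n − n·p·(1 − p)^(n−1).

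| n | r | q = 1 | q = 0.9 | q = 0.75 | q = 0.5 |
|---|---|---|---|---|---|
| 20 | 20% | 93% | 90% | 82% | 61% |
| 20 | 10% | 61% | 55% | 45% | 26% |
| 8 (only two groups at the harmful level) | 30% | 74% | 68% | 57% | 34% |

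For example, n = 20, r = 0.20, q = 0.75 gives p = 0.15 and 1 − 0.0388 − 0.1368 = 0.824.

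**2. What the group-of-4 reviews would see.** These reviews look at all adverse events. The chance that one group of 4 holds 2 or more VOCs is g = 1 − (1 − r)^4 − 4r(1 − r)^3. The chance that at least one of k groups does is 1 − (1 − g)^k.
- r = 20%, k = 5: g = 0.1808; 1 − 0.8192^5 = 63%.
- r = 10%, k = 5: g = 0.0523; 1 − 0.9477^5 = 24%.
- r = 30%, k = 2: g = 0.3483; 1 − 0.6517^2 = 58%.

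Under the larger assumed risks, then, some review would usually have such a cluster in front of it. At 10% risk it usually would not.

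**3. False halts if every VOC counts.** With a constant hazard, the rate is −ln(1 − 0.60) = 0.916 per year. Over h hours, p = 1 − exp(−0.916·h/8766).
- 24 hours: p = 0.00251, P(2 or more of 20) = 0.12%.
- 35 hours: p = 0.00365, P = 0.24%.
- If rates vary between patients (assumed gamma, shape 1 to 0.5, keeping 60% with at least one event per year): 0.3% to 0.9% at 24 hours, 0.6% to 1.8% at 35 hours.
- Assumed 5 times the rate: 2.5% at 24 hours, 4.5% to 5.0% at 33 to 35 hours.
- Assumed 10 times the rate: 8.7% at 24 hours, 15% to 16% at 33 to 35 hours. With q = 0.5 the latter would be 4.5% to 4.9%.

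The higher multiples are shown because the study's definition of VOC, a facility visit with treatment for pain, may be wider than the severe VOC behind the cited rate.

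**The case against.** The strongest reply is that the literal reading is not the natural one. A trigger with its own count, time window and causality-free definition looks designed to work without attribution, and a fixed window adds little if attribution is required as well. That stands as evidence of intent. It does not change the text, and a mandatory halt rule should not need its intent inferred.

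A reader might go further and infer that the VOC halt could rarely or never fire, because a disease-typical event will seldom be rated probable or definite. The documents do not support this. That limit is stated for determining DLT. If the Section 9.2.4 meaning applies, only remote and unrelated VOCs drop out. Remote calls for poor timing, which hardly fits an event within 24 hours of dosing. Unrelated calls for onset before dosing or a cause lying wholly elsewhere. On that reading q is close to 1. Entry at medical baseline with no VOC in the past 14 days may push q the same way.

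A reader might also infer that nothing else would catch a cluster. That is wrong too. The Medical Monitor takes part in every review, the Synopsis requires consensus on safety before proceeding and says that site safety concerns will be shared, SAEs are reported whatever their relatedness (Section 7.3), and discretionary halts remain. These safeguards are partial. The reviews are by site and group. Section 6.2.5 words the sharing more narrowly ("Any individual site safety concerns discussed, that could have a more global impact, will be shared among all participating sites"), and it bases the next dose on effect data when no DLT is seen. None of them is an automatic VOC count.

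Finally, restricting halts to related events is defensible for a common event. If background VOC really were 10 times the cited rate, the filter would prevent some false halts.

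**Conclusion.** The point holds as a drafting defect in a mandatory safety rule and should be fixed. As written, a VOC rated remote or unrelated does not count toward the halt, one rated possible may or may not, and the start of the 24-hour window is not fixed.

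The size is uncertain and rests wholly on assumed r and q. At q = 0.9 the loss is about 3 points (93% to 90%) for 20 subjects at 20% risk; at q = 0.5 it is about 32 points (93% to 61%). The documents do not say where q lies. The other reviews recover part of any loss, more when the risk is high. Confidence is medium: the wording is certain, the practical effect is not.

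**What to change.** Take the VOC bullet out from under the lead-in and give it its own sentence: any VOC within 24 hours of either dose, in at least 2 subjects across all sites, triggers the temporary halt regardless of investigator attribution. Causality is then judged in the review that follows.

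This takes one sentence in a protocol amendment. The price is a few more false halts, each a temporary pause for review: about 0.1% to 0.24% at the cited severe-VOC rate, and about 15% to 16% only if background VOC is an assumed 10 times as frequent and the window runs from either dose.
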